### Randomization

2.3

Following transfer to the NICU ward, eligible patients will be randomly assigned to two groups (ultrasound group, control group) in a 1:1 ratio. Randomization will be conducted using a predetermined random number table generated by an independent statistician using computer software (R software) and concealed within sealed opaque envelopes. For multiple births, randomization will be performed individually.

### Quality control

2.4

This trial adheres to the requirements of the Ethics Committee and will be conducted under the supervision of the Ethics Committee of the participating institution. Researchers are obligated to diligently complete the case report forms with accuracy, detail, and honesty, ensuring the authenticity and reliability of the recorded information. All observations and findings during clinical validation will be verified to guarantee data reliability, and all conclusions drawn from clinical validation will be rooted in original data. Appropriate data management measures will be implemented throughout clinical validation and data processing. Data entry into the SPSS version 20.0 software (Armonk, NY: IBM Corp) from the case report forms will be double-checked by two individuals.

### Blinding

2.5

In this study, as the administration of the first dose of PS depends on the initial lung ultrasound results, ultrasound physicians and neonatologists will be informed of the infant's group assignment at the beginning. However, subsequent ultrasound results after the first dose will not be disclosed to the clinical team to prevent any influence on the assessment of indications for the second dose of PS. In addition, blinding will be implemented for the members involved in outcome assessment and data analysis to reduce bias.

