**Figure 1 F1:**
[figure not shown]
Fowchart of participant selection and treatment.

All very preterm infants will undergo antenatal consultations before birth. Neonatologists will engage in thorough discussions with the parents of premature infants, informing them about the risks associated with premature birth at this GA and outlining the treatment process post-birth. Before delivery, a neonatal resuscitation team comprising neonatal and obstetric specialists will be established. Following delivery, premature infants will be transferred within the hospital using transport incubators, and a T-piece resuscitator will be utilized during the transfer process. Within 1 h after birth, all enrolled infants will undergo lung ultrasonography, and those meeting the diagnostic criteria will receive PS as per the trial protocol. Subsequently, they will undergo regular lung ultrasound monitoring until discharge or at 36 weeks corrected age (CA).

Centers participating in the study routinely use lung ultrasonography. Two ultrasound physicians and five neonatologists will participate in this study. Both ultrasound physicians have received comprehensive training in lung ultrasonography and LUS application. Lung ultrasonography will be performed by two ultrasound physicians, who each have more than 2 years of experience in neonatal lung ultrasound and have received systematic training before the study, including study protocols, lung ultrasound scoring, and interpretation of lung ultrasound images. In order to ensure the consistency of scoring results, the two doctors will respectively determine the LUS based on ultrasound images. If the scores are consistent, the results will be recorded. If the score difference is ≥2, the final score will be determined by the two doctors after discussion.

Other research personnel have completed standardized training, including familiarization with the trial protocol, methods of recording case records, and criteria for assessing complications.

Lung ultrasonography will be conducted using the Mindray M9 ultrasound system equipped with a linear, high frequency (10–15 MHz) transducer.

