#### Control group

2.7.2

In cases where clinical diagnosis confirms NRDS, PS will be administered at a dosage of 200 mg/kg (Poractant Alfa, Curosurf®). LISA will be employed for infants in a non-invasive ventilation state, while those in an invasive ventilation state will receive PS via endotracheal tube. If clinical manifestations do not meet the diagnosis of NRDS, PS will not be administered.

All enrolled infants will undergo lung ultrasound scoring at 24 h, 3 days, 7 days, 14 days, 28 days, and 36 weeks CA (prior to discharge) (with scoring results withheld from the clinical team).

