### Therapy

2.8

Lung ultrasound procedure: The lungs will be partitioned based on the six-region method in the pulmonary ultrasound guidelines. Each lung will be divided into three regions: anterior, lateral, and posterior lung area. To do this, the anterior axillary line and the posterior axillary line will be used as boundaries. Both lungs will be divided into a total of six regions (19). An ultrasound probe perpendicular to the intercostals will be used to scan each area from the top to bottom and score it. A score of 0–3 (as proposed by Bratet al.) will be assigned to each scan area based on the ultrasound detected pattern; in the case of different score patterns in the same area, the worst will be selected (Figure 2) (14).

RDS lung ultrasound diagnostic criteria: (1) Lung consolidation with air bronchograms: this is the most crucial ultrasound manifestation of RDS, characterized by: (i) The degree and extent of consolidation correlate with disease severity. Mild RDS may exhibit consolidation limited to the subpleural areas, appearing focal and small in scope, while severe RDS demonstrates expanded consolidation areas, extending into deeper lung fields; (ii) consolidation may be observed in different lung fields on bilateral lungs or restricted to certain intercostal spaces on one side; and (iii) air bronchograms present as dense, snowflake-like, or spot-like patterns, with the consolidation area showing heterogeneous hypoechoic areas that are easily distinguishable from surrounding lung tissue; (2) Abnormal pleural lines and disappearance of A-lines; (3) Non-consolidated areas show changes resembling interstitial syndrome; (4) Bilateral points: these may be present during the acute phase of mild RDS or the recovery phase of severe RDS; and (5) pleural effusion: infants may exhibit varying degrees of unilateral or bilateral pleural effusion (19).

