### Outcome measures

2.9

The primary outcome measure for this study is the duration of mechanical ventilation (both invasive and non-invasive) during hospitalization in the ultrasound and control groups. Secondary outcome measures encompass: (1) the utilization rate of PS in both groups; (2) the proportion of infants receiving the first dose of PS early (within 3 h after birth) and the time from birth to the initial PS administration; (3) the oxygen concentration and the worst oxygenation index (OI) at different time points following PS administration; (4) LUS at various intervals following PS administration (at 3 days, 7 days, 14 days, 28 days, and before discharge/at 36 weeks CA; and (5) the incidence rates of major complications in preterm infants such as BPD, intraventricular hemorrhage (IVH), retinopathy of prematurity (ROP), and necrotizing enterocolitis (NEC).

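### Section 2.5 promises blinded outcome assessment, but follow-up LUS (secondary outcome 4) is scored by the two ultrasound physicians who are told the allocation

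*Protocol article*

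**What the plan says.** - **Blinding claim.** Protocol article, section 2.5 (Blinding): "blinding will be implemented for the members involved in outcome assessment and data analysis to reduce bias". No outcome is excepted.
- **Who knows the arm.** The same section: "ultrasound physicians and neonatologists will be informed of the infant's group assignment at the beginning". The reason given is that the first surfactant dose depends on the initial scan.
- **Who scans and who scores.** Section 2.1 (Study design, text after Figure 1): "Lung ultrasonography will be performed by two ultrasound physicians", and then "the two doctors will respectively determine the LUS based on ultrasound images". No other reader is named.
- **LUS is an outcome.** Section 2.9 (Outcome measures) lists as secondary outcome (4) "LUS at various intervals following PS administration", at 3, 7, 14 and 28 days and before discharge or at 36 weeks corrected age.
- **Both arms are scored.** Section 2.7.2: "All enrolled infants will undergo lung ultrasound scoring at 24 h, 3 days, 7 days, 14 days, 28 days, and 36 weeks CA".
- **How a region is scored.** Section 2.8 (Therapy) grades each region 0 to 3 by pattern, and "in the case of different score patterns in the same area, the worst will be selected".
- **What is masked.** Sections 2.5, 2.7.1 and 2.7.2 withhold later results from the clinical team. Limitation (1) in the Discussion says that masking the ultrasound physicians is impractical and repeats that later results are kept from clinicians.

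**The concern.** The people who produce the LUS outcome are the people who know the arm. The withholding of later results runs from reader to clinician. It protects treatment decisions after the first scan, but it does not stop the reader's knowledge of the arm from entering the score.

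LUS is a visual grading, so knowing which infants were managed by the strategy under test can move borderline grades. If both readers lean the same way, the between-arm difference in LUS mixes a treatment effect with a reading effect, and the analysis cannot separate them. Someone relying on section 2.5 alone would also take this outcome to be assessed blind.

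**Working it through.** **1. The statements side by side**

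| Question | Answer in the protocol article | Where |
|---|---|---|
| Are outcome assessors blinded? | Yes, without exception | 2.5 |
| Is follow-up LUS an outcome? | Yes, secondary outcome (4) | 2.9 |
| Who determines LUS? | The two ultrasound physicians | 2.1 |
| Do they know the arm? | Yes, from the beginning | 2.5; Discussion, limitation (1) |
| Are separate readers, coded images or readers masked to arm described? | No | – |

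The second, third and fourth rows together make the assessors of outcome (4) unblinded. The first row says that they are blinded. Both cannot be true of LUS.

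**2. Does the stated reason cover follow-up scans?** The first score feeds the surfactant decision in the ultrasound arm, so it must be read at once and its reader may need to know the arm. Later scores are withheld from clinicians and drive no treatment decision. Nothing in the stated reason requires them to be read at once or with the arm known.

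**3. Does double reading help?** It reduces individual error. It does not remove a lean shared by two readers who both know the arm.

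**4. Is the sample size touched?** Inputs from section 2.12: means 96 and 86 h, SD 12 h, α 0.05 (taken as two-sided), power 80%.
- Normal approximation: n = 2 × (1.960 + 0.842)² × (12/10)² = 22.6, so 23 per group.
- Noncentral t: 23.6, so 24 per group, with power 80.7%.
- Inflation: 48 ÷ 0.80 = 60.

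The stated 24 per group and 60 in total reproduce. They rest on ventilation duration, not LUS, so this point leaves them unchanged.

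**5. What a shared lean would do (illustration only).** The documents give no SD for LUS, no reader agreement and no estimate of bias. Assume no true difference and a systematic reading shift of b SD between arms. A two-sided 5% t-test has noncentrality b × √(n/2), and rejects as follows:

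| b (assumed) | 24 per arm | 30 per arm |
|---|---|---|
| 0 | 5% | 5% |
| 0.1 | 6.3% | 6.7% |
| 0.2 | 10.4% | 11.9% |
| 0.3 | 17.5% | 20.8% |
| 0.5 | 39.6% | 47.8% |

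The table shows that such a shift is not diluted by recruiting more infants. It does not show that any of these shifts is likely.

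**The case against.** **The authors disclose it.** The trial is labelled non-blinded, section 2.5 itself says that the ultrasound physicians know the group, and limitation (1) concedes it. This stands as far as it goes: nothing is concealed. But the limitation neither withdraws nor narrows the blinding sentence. It does not say that LUS is assessed unblinded, and the mitigation it offers protects clinicians' decisions, not the reading.

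**The sentence may concern other staff.** Section 2.1 separates the ultrasound physicians from the other research personnel, who are trained in complication criteria. Table 1 puts LUS in its own row, above the block for outcomes assessment. That may be what was meant, and blinding may well hold for those other outcomes. But section 2.9 lists LUS as a secondary outcome and section 2.5 makes no exception, so the text as it stands covers LUS.

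**An article may leave image handling to the full protocol.** That is fair for operational detail. Here, however, the article names the readers, says that they know the arm and claims blinded assessment. That conflict is in the article itself.

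**Stronger readings that a reader might infer.** One is that the LUS comparison is biased towards the ultrasound arm by some definite amount. The documents support neither a direction nor a size. Another is that a lean would pass unnoticed because reader differences below 2 points are not sent to discussion. That does not follow: discussion resolves disagreement between readers, and a shared lean produces none.

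**Conclusion.** The point holds for secondary outcome (4) only. As written, the blinded-assessment statement in section 2.5 is incorrect for follow-up LUS, and the reason given for unblinding does not extend to those scans. The comparison is open to reader bias whose direction and size cannot be determined from the documents.

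The primary outcome, the sample size and the withholding of later results from clinicians are not affected by this point. It should be corrected because the outcome is measured repeatedly in both arms, depends on judgement, and can be largely protected at low cost.

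The conclusion assumes that the two physicians named in section 2.1 score the follow-up scans as well as the first. The article names nobody else.

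**What to change.** 1. **Reading.** Store every follow-up scan as clips coded without arm, identity or date. Have the same two physicians score them later, independently and in random order. Section 2.1 already bases scoring on images, so no extra scan or reader is needed.
2. **Section 2.5.** State that image acquisition and first-scan scoring are unblinded, and that follow-up scoring is masked as far as coding allows. Name the other outcomes that are assessed blinded.
3. **If coded reading is not done.** Limit the blinding sentence to the outcomes it covers, and report LUS as assessed unblinded.

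**Cost.** Clip storage, relabelling and delayed score entry, for at most 60 infants × 5 outcome visits = 300 scans. The third option costs one sentence.

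**What remains.** The protection is partial. The physicians who acquired the images may recognise some infants, and what is captured is still chosen by someone who knows the arm. Follow-up LUS should therefore not be described as fully blinded even after the change.

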### Assessment points

2.6

The main assessment and recording of the infants’ indicators will occur at the following time points (Table 1).

**Table 1 T1:** Neonatal assessment chart.

Measure	Assessment point							
	Allocation within 1 h after birth	4–10 h after PS	24 h	3 days	7 days	14 days	28 days	36 weeks CA/discharge
LUS	×	×	×	×	×	×	×	×
Clinical index								
Silverman Anderson score	×	×	×	×	×	×	×	×
Respiratory support mode	×	×	×	×	×	×	×	×
Ventilator parameters	×	×	×	×	×	×	×	×
Medication use of PS	×		×					
Outcomes assessment								
NIV (hours)								×
IMV (hours)								×
Supplemental oxygen (days)								×
PS (%)								×
Early PS (%)								×
Birth to the application of 1st PS (min)								×
LOS								×
Costs associated with hospital care								×
Complications								
hsPDA (%)								×
BPD (%)								×
IVH (%)								×
NEC stage I or II (%)								×
ROP (%)								×

NIV, non-invasive ventilation; IMV, invasive mechanical ventilation; Early PS, pulmonary surfactant administered within 3 h after birth; LOS, length of stay; hsPDA, hemodynamically significant patent ductus arteriosus; IVH, intraventricular hemorrhages; BPD, bronchopulmonary dysplasia; NEC, necrotizing enterocolitis; ROP, retinopathy of prematurity.

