#### Exclusion criteria

2.2.2

Infants who meet any of the following criteria will be excluded: (1) infants who have received PS treatment in the delivery room or external setting after birth; (2) infants with known or confirmed congenital abnormalities, especially cardiopulmonary deformities during diagnosis or treatment; (3) presence of severe complications at birth (severe asphyxia, hemorrhagic shock, pneumonia, pneumothorax, early-onset sepsis, and pleural effusion) or other diseases not caused by PS deficiency; (4) infants who die within 72 h after birth, are transferred to another hospital for surgery, or have incomplete data; and (5) those with families who do not consent to participate in this study.

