### Data collection and diagnoses

2.10

Patient demographic data mainly include: (1) GA, birth weight, singleton or multiple births, sex, prenatal steroid use, mode of delivery, presence of intrauterine distress, and maternal pregnancy complications; and (2) Apgar scores at 1 min, 5 min, and 10 min, as well as umbilical cord blood gas analysis.

Clinical information at each time point (at admission, 1 h after birth, 4–10 h after PS administration, 24 h, 72 h, 7 days, 14 days, 28 days, and before discharge or at 36 weeks CA) include (1) timing, dosage, and method of the initial PS administration; (2) SAS, respiratory machine mode, oxygen saturation index, and FiO_2_ levels at each time point; and (3) LUS at each time point. LUS will collect individual scores for each lung field as well as the total score.

Complications and outcomes: (1) Respiratory complications: this includes the occurrences of infectious pneumonia, pneumothorax, pulmonary hemorrhage, and BPD, along with their severity grading; (2) Cardiovascular complications: specifically, hemodynamically significant patent ductus arteriosus (hsPDA); (3) Other complications in premature infants: these encompass IVH, periventricular leukomalacia, NEC, late-onset sepsis, ROP, intrauterine growth restriction, and more; and (4) Length of hospital stay and associated costs.

BPD diagnosis will adhere to the 2018 National Institute of Child Health and Human Development (NICHD) classification. Diagnosis of hsPDA will rely on clinical signs and echocardiography (20). IVH and white matter injury will be diagnosed via cranial ultrasound, with IVH graded using the Papile classification (21). NEC staging will follow modified Bell criteria (22). ROP diagnosis and staging will be based on fundoscopic examinations conducted by ophthalmologists.

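### Table 1 limits the NEC outcome to stages I and II, while sections 2.9 and 2.10 set no stage limit; read literally, the row omits the infants with worse NEC

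*Protocol article*

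**What the plan says.** Three places in the protocol article bear on how NEC is counted.

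- **Section 2.6, Table 1.** The complications block has five rows, all marked for the last assessment column (36 weeks corrected age or discharge). The NEC row reads "NEC stage I or II", as a percentage. The rows for hsPDA, BPD, IVH and ROP carry no stage or grade.
- **Section 2.9.** The fifth secondary outcome is "the incidence rates of major complications in preterm infants such as BPD, intraventricular hemorrhage (IVH), retinopathy of prematurity (ROP), and necrotizing enterocolitis (NEC"), with no stage limit.
- **Section 2.10.** The non-respiratory, non-cardiac complications are listed as follows: "these encompass IVH, periventricular leukomalacia, NEC, late-onset sepsis, ROP" and others. NEC again has no limit. The same section adds that "NEC staging will follow modified Bell criteria".

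A fourth place affects whether an infant is in the comparison at all. Section 2.2.2 excludes infants who "are transferred to another hospital for surgery", without giving the reason for surgery or the timing relative to randomisation.

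**The concern.** The same secondary outcome has two definitions, and the narrower one is narrow at the wrong end. A severity limit on a complication usually sets a floor, so that mild or doubtful cases do not dilute the rate. The Table 1 label sets a ceiling: it keeps the lowest stage and leaves out whatever lies above stage II. That sits badly with section 2.9, which presents NEC as a major complication.

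If the case report form or the results table is built from Table 1, an infant whose disease goes beyond stage II is entered as not having the tabulated outcome. An arm with such an infant then shows a lower NEC rate than it had. With few NEC cases expected among 60 infants, one or two reclassified infants could visibly change the reported comparison.

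The surgical-transfer exclusion raises a related but separate question. An infant who leaves for NEC surgery after randomisation could be dropped from the analysis, and the NEC event would go with the infant.

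**Working it through.** **No stated figure to reproduce.** The article gives no expected NEC rate and no power for NEC. Its only calculation, in section 2.12, uses a 10 h difference (96 against 86 h) with SD 12 h, two-sided alpha 0.05 and 80% power. A t-test solution gives 23.6, rounded up to 24 per group, which matches the article, and 48 / 0.80 = 60. NEC is not an input, so nothing here changes with its definition.

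**The definitions side by side.**

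| Place | NEC as written | Worst stage I or II | Worst stage above II |
|---|---|---|---|
| Table 1 | stage I or II | counted | not counted |
| Section 2.9 | no limit | counted | counted |
| Section 2.10 | no limit, modified Bell staging | counted | counted and staged |

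The definitions disagree only in the last column. Nothing in the article explains the limit or places higher-stage NEC in another outcome.

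**A further ambiguity in the row.** If infants are classified by worst stage, a case that progresses beyond stage II leaves the numerator. If they are classified by any stage passed through, the same infant may still count. Table 1 does not say which applies, so two assessors could derive different rates from the same records.

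**Size per infant.** Section 2.12 plans 30 infants per arm. If k infants in an arm have a worst stage above II, the Table 1 rate in that arm is lower than the all-stage rate by k/30:

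- k = 1: 1/30 = 3.3 percentage points
- k = 2: 2/30 = 6.7 percentage points

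**How many infants might be affected.** The article gives no basis for this, so the following is an assumption shown as a range. Suppose NEC of any stage occurs in 5% to 15% of the 60 infants and 10% to 40% of those cases are above stage II.

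- Low end: 60 × 0.05 = 3 cases; 3 × 0.10 = 0.3 omitted; 2.7 counted.
- High end: 60 × 0.15 = 9 cases; 9 × 0.40 = 3.6 omitted; 5.4 counted.

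The omitted number runs from practically none to about four across both arms.

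**The transfer exclusion.** Sections 2.3 and 2.7 place randomisation at admission to the NICU ward, and section 2.7 puts that transfer within 15 min of birth for infants who recover successfully. A later transfer for surgery therefore falls after randomisation. Removing one of x NEC cases from an arm of 30 takes the infant out of both numerator and denominator, so the rate falls by x/30 − (x − 1)/29 = (30 − x)/870. For x = 1 this is 29/870 = 3.3 percentage points; for x = 3 it is 27/870 = 3.1. The effect per infant is about the same as under the Table 1 label. An infant already removed cannot also be miscounted in the row, so any one case is lost by one route only.

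**The case against.** The strongest objection is that Table 1 does not define the outcome. It is a schedule of assessments, whereas outcomes are set in section 2.9 and diagnoses in section 2.10, and neither limits NEC by stage. The table is visibly incomplete: it omits pneumothorax, pulmonary hemorrhage, periventricular leukomalacia and late-onset sepsis, all of which section 2.10 collects, and the oxygenation index from section 2.9. On this reading, an infant above stage II is staged, recorded and counted, and the label is a slip. This largely stands as an account of what was probably meant. It does not remove the conflict, because the article never says which place governs and the table is a natural template for the case report form.

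Stronger readings are tempting but unsupported:

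- **That the comparison is biased in favour of the arm with worse disease.** This needs the restricted label to be used in the analysis and cases above stage II to differ between arms. Nothing in the article shows such a difference. If they are balanced, the NEC rate is incomplete in both arms, with no direction.
- **That surgical NEC is lost twice.** The label and the exclusion are alternative routes. Section 2.2.2 does not mention NEC, and nothing says that NEC surgery means leaving this tertiary referral hospital.
- **That a definite number of cases will be lost.** No rate is given, and the low end of any reasonable range is close to zero.

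It is also true that the article does not list the Bell stages. The point needs only that a stage above II exists, which a limit to stages I and II itself implies.

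**Conclusion.** The inconsistency is real. Table 1 gives a stage-limited definition of NEC, sections 2.9 and 2.10 give an unlimited one, and the Table 1 version followed literally would understate the NEC rate in any arm with an infant whose worst stage is above II. The size is 3.3 percentage points per such infant, assuming all 30 per arm are analysed and infants are classified by worst stage. The number of such infants is unknown and probably small.

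Whether the error goes beyond the table label cannot be settled from the article. Directional bias is not shown. The possible removal of infants transferred for NEC surgery is a separate weakness, conditional on such transfers taking place. NEC is one of several complications within a secondary outcome, and the primary outcome and sample size are untouched. The matter should be corrected before outcomes are tabulated, but it does not threaten the trial's main conclusion.

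**What to change.** Change the Table 1 row to NEC of any stage, classified by the worst modified Bell stage reached by the final assessment, so that it agrees with section 2.9. Report stage II or higher as a second line, derived from the same staging. If the stage I and II limit was deliberate, the article should say why and where higher stages are reported.

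Add one sentence stating that an infant transferred for surgery because of NEC after randomisation stays in the randomised arm and counts as an NEC event, and qualify the transfer exclusion in section 2.2.2 accordingly.

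The cost is one table row and one or two sentences. Staging is already planned in section 2.10, so infants who stay need no new data item. For a transferred infant, the worst stage may need to be obtained from the receiving hospital, but the event itself can be counted from the reason for transfer.
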